#### 5.2 Secondary objectives

II) To study internalization and implementation factors such as reach and dose of the medical device across 6 months.

III) To explore the impact of three different levels of digital support for healthy habits on reaching self-identified goals, dietary and physical activity habits, and mental health after 6 months.

IV) To explore determining response of sociodemographic factors in meeting the self-identified goal, dietary and physical activity habits, mental health, and well-being.

V) To evaluate the intended mediators (engagement with the service, improved motivation, self-efficacy, and reduced perceived barriers) of the medical device on achieving the self-identified goal, improved dietary and physical activity habits, mental health, and well-being.

VI) To explore what app functions and features mediate improvements of the medical device on behavior change, mental health, and well-being.

VII) To explore the engagement of using the digital service and adherence to behavior change across 24 months.

VIII) To explore the patterns of achieving the self-identified goal, change in motivation, dietary and physical activity habits, mental health, and well-being across 24 months.

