### 7.3 Analytical procedures

Change in the endpoint well-being (as total score) and the intermediate outcomes dietary habits, physical activity, and mental health, will be analysed across time and between groups using mixed model for repeated measures, and reported as estimates with confidence intervals. The model will include intervention level and time (0, 6, 12, 18 and 24 months).

To investigate correlations and associations of demographic factors and user engagement with behavior change, mental balance, and well-being, structural equation modelling and mixed models will be applied.

Regression analysis and mixed models will be applied to evaluate mediating factors and responsiveness. These analyses will explore if high levels of motivation, self-efficacy and reduced perceived barriers mediates improvements in reaching the self-identified goal, behavior, mental health, and well-being and whether improvements in motivation, behavior, and mental health mediate well-being. Cut off values for the intermediate outcomes will be derived based on baseline values and findings from similar studies.

The threshold for statistical significance will be set at  $p < 0.05$ .

Qualitative data (chat groups and dialogues with included actors) will be analyzed by content analysis (46).

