### 7.4 Sample size calculation

The endpoint well-being will be assessed using the WHO-5 Well-being Index (34). In our pilot study the mean score at baseline was 55. The instrument has to our knowledge not been applied on a general Swedish population. In Danish general population surveys, the mean WHO-5 score was 60-70 ( $sd=19.0-19.9$ ) (36, 47, 48). A change of 10-20 points in WHO-5 has been proposed as a clinically relevant change (36, 49). In up-scaled interventions 60% lower effects are expected (50). We therefore aim at a difference of 12 points in the score between intervention groups and control group as well as between baseline and 6 months. A fluctuation in well-being is considered normal (36), subjects with well-being score  $>70$  are not expected to improve and will be excluded from the analysis. In the pilot study 21% of participants reached 70 points at baseline.

Desirable sample size was calculated to detect an effect of 12 points (36, 51) based on the assumption of two-tailed testing, an alpha error  $\alpha=0.05$  and power  $1-\beta=0.90$  and  $sd=19.9$  (48). To detect a medium standardised effect size of 0.5 (Cohen's d) for the primary outcome well-being at 6 months a sample size of at least 25 subjects per group is recommended. Expected drop-out rate due to withdrawal and lost to follow-up at six months is 75 %. Based on the expected drop-out rates and on excluding 20% from the analysis due to baseline score  $>70$ , we need to recruit at least 500 subjects to assure 25 subjects in each intervention arm. In the control group we assume subjects to be excluded based on using a digital product for behavior change and strive to include 200 subjects.

The secondary outcomes are exploratory due to the person-centred design of the service. The subjects will set individual goals and possibly change goals during the intervention. Likewise, habits and behavior change are largely changeable due to circumstances. The current research is not immense enough to guide a decision for minimal expected effects when individual goals are set (e.g., reducing weekly servings of red meat). A larger sample size than what is required for the primary

endpoint well-being is desired. Similarly, the secondary analyses of mediating factors and responsiveness require a large sample size. We therefore aim to include 5000 subjects.

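### Section 7.3 plans cut-offs for the intermediate outcomes, drawn partly from the study's own baseline values, without saying whether they replace the full scores or when they are fixed; if they dichotomise the scores, at least about 36% of the information is lost.

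*Protocol*

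**What the plan says.** Section 7.3 has two places that bear on the intermediate outcomes (dietary habits, physical activity, mental health). Its first paragraph says that change in these outcomes, and in well-being as a total score, "will be analysed across time and between groups using mixed model for repeated measures, and reported as estimates with confidence intervals". No cut-off appears there.

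The third paragraph turns to mediation: "Regression analysis and mixed models will be applied to evaluate mediating factors and responsiveness". It continues "These analyses will explore if high levels of motivation, self-efficacy and reduced perceived barriers mediates improvements in reaching the self-identified goal", followed by behaviour, mental health and well-being, and ends with "Cut off values for the intermediate outcomes will be derived based on baseline values and findings from similar studies". No value, quantile, instrument, analysis or date is attached to that sentence.

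These analyses serve objectives V and VI in section 5.2 (objective V begins "To evaluate the intended mediators (engagement with the service, improved motivation, self-efficacy, and reduced perceived barriers) of the medical device") and hypothesis 4 in section 5.3. Section 7.4 gives them as one reason for the target of 5000: "Similarly, the secondary analyses of mediating factors and responsiveness require a large sample size". The same section calls the secondary outcomes exploratory and states no power for them.

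**The concern.** Several of the outcomes concerned are collected as multi-item scores or counts: KEDS, OLBI, ISI, hours of sleep, daily steps and, in a subsample of 300, accelerometer minutes. The mixed model of the first paragraph needs no threshold, so the natural use of the cut-offs is in the mediation and response analyses beside which they stand. Three things follow if that is so.

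- **Information.** Splitting a score in two discards the distances within each half. Section 7.4 asks for a large sample partly for these analyses, and a split gives part of that sample away. The protocol offers no reason for a cut.
- **Meaning of response.** If response is defined as crossing one fixed level, a user just on the wrong side of it responds with a trivial change, while a user far from it can improve a great deal and still count as a non-responder.
- **Timing.** Users join as they sign up, and section 15 allows up to 5 years to reach 5000, while follow-up starts within months of joining. The full baseline distribution will therefore be known only after many early users have follow-up data. Nothing says the cut-offs are fixed before those data are examined.

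**Working it through.** **1. The plan's own power figure.** The only power in the protocol is in section 7.4, for WHO-5 at 6 months: "Desirable sample size was calculated to detect an effect of 12 points", "based on the assumption of two-tailed testing, an alpha error" of 0.05, power 0.90, SD 19.9, also expressed as d = 0.5, giving 25 per group. With n per group = 2 × [(1.960 + 1.282)/d]²:

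- d = 12/19.9 = 0.603 gives 58
- d = 0.5 gives 85

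The stated 25 is not reproduced; it has 57% and 42% power respectively. That is a separate matter. What counts here is that the 90% belongs to WHO-5, which is the endpoint, is analysed as a total score and is not cut. It is not a figure for mediation or responsiveness. Below, 90% is only a reference point.

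**2. Loss from cutting one normal score.** With a share p of subjects on one side of cut c, the information kept relative to the full scale is φ(c)²/[p(1 − p)]. At the median this is 0.3989²/0.25 = 0.637, a loss of 36%. An analysis with 90% power on the full scale then has power Φ(3.242 × √kept − 1.960); at the median, Φ(3.242 × 0.798 − 1.960) = Φ(0.626) = 73%.

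| Cut | Information kept | Power if 90% on full scale | Sample needed to recover 90% |
|---|---|---|---|
| 50/50 | 0.637 | 73% | × 1.57 |
| 40/60 | 0.622 | 72% | × 1.61 |
| 30/70 | 0.576 | 69% | × 1.74 |
| 20/80 | 0.490 | 62% | × 2.04 |
| 10/90 | 0.342 | 47% | × 2.92 |

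The protocol does not place the cut, so the range is shown. If the mediator were median-split as well, the figure would be Φ(3.242 × 0.637 − 1.960) = 54%. The cut-off sentence names intermediate outcomes only, so this last case goes beyond the text.

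**3. At the planned scale.** Assume the 75% drop-out and 20% exclusion of section 7.4 apply here too: 5000 × 0.25 × 0.80 = 1000 analysable. Power for a correlation r is about Φ(r√n − 1.960).

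- r = 0.10, full scale: Φ(3.162 − 1.960) = 89%
- r = 0.10, median cut: Φ(3.162 × 0.798 − 1.960) = 71%
- Correlation detectable with 90% power: 3.242/√1000 = 0.103 on the full scale, 0.128 after a median cut

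If all 5000 could be analysed, r = 0.10 would have above 99.9% power either way. In the other direction, section 7.1 limits the intermediate outcomes to users with a goal in that area, so the number per outcome will be below 1000.

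**4. Large effects.** With 1000 split evenly over three service levels (about 333 each), a difference of d = 0.5 keeps 98% to 99.9% power for cuts anywhere from the 20th to the 90th percentile (two-proportion test). The loss matters for small effects and for small goal-specific subsets.

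**The case against.** The strongest reply is that the text does not say the scores are replaced. It says that cut-offs will be derived; descriptive or supplementary use fits, section 7.2 already foresees counts for dichotomous variables, and the first paragraph of 7.3 models the intermediate outcomes without any cut. This stands: dichotomisation in the mediation analyses is the likely reading, not a stated fact.

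A reader might also infer that the power of these analyses drops from 90% to 73%. The document does not support that. It gives no power, effect size or sample size for them, so 73% holds only for an analysis that would otherwise have 90%.

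A reader might infer that response is bound to depend on the starting value. That is so for a fixed level. If baseline values means each user's own baseline, and the cut applies to change, it is not shown. Nor is a cut taken from baseline data driven by outcomes in itself; the weakness is that no time of fixing is given.

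Objective IV should not be drawn in either: demographic factors are handled mainly in a separate paragraph of 7.3 that mentions no cut-off. Finally, dietary and activity questions and goal days per week may be categorical or far from normal, and the normal-theory loss does not carry over to them.

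One could add that thresholds are detail for an analysis plan. Their exact values are. But the protocol itself commits to deriving thresholds partly from study data, and the question is whether that commitment is a good one.

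**Conclusion.** The point holds in a limited form. Section 7.3 commits to partly study-derived cut-offs for the intermediate outcomes and leaves open both their role and the time they are fixed. If they dichotomise continuous scores in the analyses for objectives V and VI and hypothesis 4, the loss is at least about 36% of the information: 90% becomes about 73% at best, or 89% becomes 71% for r = 0.10 with 1000 subjects. This rests on normal scores, on the cut-offs being used to split them, and, for the second figure, on 1000 being analysable. The primary endpoint is not affected, the analyses are exploratory, and large effects would survive. It is a modest defect, worth correcting because a better method is available at almost no cost.

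**What to change.** Replace the cut-off sentence in section 7.3 with:

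> In the mediation and response analyses, mediators and intermediate outcomes are analysed on their full continuous or ordinal scale, adjusted for the baseline value. Any cut-off is supplementary or descriptive, uses a published threshold where one exists, and is fixed before follow-up data are examined.

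Items that are categorical by design keep their categories. The cost is one sentence and no new data. The small downside is that regression coefficients are less immediately readable than responder percentages, which can still be reported alongside.

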### 7.4 Sample size calculation

The endpoint well-being will be assessed using the WHO-5 Well-being Index (34). In our pilot study the mean score at baseline was 55. The instrument has to our knowledge not been applied on a general Swedish population. In Danish general population surveys, the mean WHO-5 score was 60-70 ( $sd=19.0-19.9$ ) (36, 47, 48). A change of 10-20 points in WHO-5 has been proposed as a clinically relevant change (36, 49). In up-scaled interventions 60% lower effects are expected (50). We therefore aim at a difference of 12 points in the score between intervention groups and control group as well as between baseline and 6 months. A fluctuation in well-being is considered normal (36), subjects with well-being score  $>70$  are not expected to improve and will be excluded from the analysis. In the pilot study 21% of participants reached 70 points at baseline.

Desirable sample size was calculated to detect an effect of 12 points (36, 51) based on the assumption of two-tailed testing, an alpha error  $\alpha=0.05$  and power  $1-\beta=0.90$  and  $sd=19.9$  (48). To detect a medium standardised effect size of 0.5 (Cohen's d) for the primary outcome well-being at 6 months a sample size of at least 25 subjects per group is recommended. Expected drop-out rate due to withdrawal and lost to follow-up at six months is 75 %. Based on the expected drop-out rates and on excluding 20% from the analysis due to baseline score  $>70$ , we need to recruit at least 500 subjects to assure 25 subjects in each intervention arm. In the control group we assume subjects to be excluded based on using a digital product for behavior change and strive to include 200 subjects.

The secondary outcomes are exploratory due to the person-centred design of the service. The subjects will set individual goals and possibly change goals during the intervention. Likewise, habits and behavior change are largely changeable due to circumstances. The current research is not immense enough to guide a decision for minimal expected effects when individual goals are set (e.g., reducing weekly servings of red meat). A larger sample size than what is required for the primary

endpoint well-being is desired. Similarly, the secondary analyses of mediating factors and responsiveness require a large sample size. We therefore aim to include 5000 subjects.

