## 7. Statistical design and analysis

### 7.1 Analysis population

For the endpoint well-being an intention-to-treat approach will be applied. By using mixed model for repeated measures all subjects with two or more measurements will be included in the analysis and manual imputation is not needed. For the intermediate outcomes dietary habits, physical activity, and mental health only subjects who have set up change goals within the area will be analysed.

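### Dropping subjects with a baseline WHO-5 above 70 produces a rise by 6 months without any effect, and the baseline-to-6-month target in 7.4 would credit that rise to the app

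*Protocol*

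**What the plan says.** The cut at 70 appears in the synopsis (1.6), among the exclusion criteria for both groups in 6.2, and in 7.4. In 1.6 and 6.2 it removes subjects from the primary analyses only. Section 7.4 ties it to the baseline score, explains that well-being fluctuates normally, and says those above 70 "are not expected to improve and will be excluded from the analysis".

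The same section aims at 12 points "between intervention groups and control group as well as between baseline and 6 months". It gives the starting levels as "In our pilot study the mean score at baseline was 55" for pilot users and, for Danish general-population surveys, "the mean WHO-5 score was 60-70".

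Section 7.3 analyses change in well-being with a mixed model for repeated measures. The named terms are intervention level and time, and month 0 is one of the time points. Section 7.1 promises intention-to-treat for well-being and says "all subjects with two or more measurements will be included in the analysis", without mentioning the cut.

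Allocation is not randomised (3.1), and controls are a sample of the general population (5.1).

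**The concern.** If scores fluctuate, some of those above 70 on one reading are there by chance, and removing them leaves a group whose chance deviations are on average negative. That group's mean moves up at the next reading whether or not the app works. The truncated month-0 score enters the 7.3 model as an outcome, so the rise appears as change over time.

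The within-group half of the 12-point aim has no comparator, so it takes the whole artefact as benefit. The comparison of change with controls removes it only if both groups regress equally. That depends on their baseline distributions, and without randomisation nothing makes these alike. The cut may also cost the small control group more subjects than the plan allows for.

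**Working it through.** **Inputs.** From 7.4: SD 19.9, cut at 70, user mean 55, general-population mean 60-70, target 12 points. Assumed, because the documents do not give them: normal scores, no true change, a baseline-to-6-month correlation r of 0.4 to 0.8, and the Danish means as a proxy for these controls.

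**The plan's own figure first.** With mean 55 and SD 19.9, the share above 70 is 1 - Φ((70 - 55)/19.9) = 1 - Φ(0.754) = 22.5% (21.5% at SD 19.0). The plan reports that 21% of pilot participants reached 70 and allows 20%, so the normal model fits the users reasonably well.

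**Regression to the mean.** With z = (70 - μ)/SD, the mean of those kept is μ - g, where g = SD × φ(z)/Φ(z). With no true change, the expected rise by 6 months is (1 - r) × g. For users, g = 19.9 × 0.300/0.775 = 7.7, so the kept mean is 47.3 and the rise at r = 0.6 is 0.4 × 7.7 = 3.1.

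| Group mean | Share above 70 | Mean after cut | g | Null rise at r = 0.8 / 0.6 / 0.4 | Users minus controls, change |
|---|---|---|---|---|---|
| 55 (users) | 22.5% | 47.3 | 7.7 | 1.5 / 3.1 / 4.6 | n/a |
| 60 (controls) | 30.8% | 49.9 | 10.1 | 2.0 / 4.0 / 6.1 | -0.5 / -1.0 / -1.4 |
| 65 (controls) | 40.1% | 52.2 | 12.8 | 2.6 / 5.1 / 7.7 | -1.0 / -2.0 / -3.1 |
| 70 (controls) | 50.0% | 54.1 | 15.9 | 3.2 / 6.4 / 9.5 | -1.6 / -3.3 / -4.9 |

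A control mean of 55 gives a difference of 0 at every r. A simulation at r = 0.6 with scores in 4-point steps bounded at 0 and 100 gave rises of 3.08 (mean 55) and 5.16 (mean 65), and about 0 without the cut.

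**Against the target.** 1.5/12 = 13% and 4.6/12 = 39%.

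**The level contrast.** Hypothesis 1 (5.3) compares mean scores at 6 months. At r = 0.6 and a control mean of 65, the null difference is 55 - 65 = -10.0 without the cut. With it, the difference is (55 - 0.6 × 7.7) - (65 - 0.6 × 12.8) = 50.4 - 57.3 = -6.9. At control means of 60 and 70 the figures go from -5.0 to -3.6 and from -15.0 to -10.1. Here the cut narrows the null gap.

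**Control numbers.** Of 200 controls, the cut would keep about 138, 120 or 100 at means of 60, 65 or 70. For controls, 7.4 mentions only losses from use of another digital product.

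**The case against.** The best defence is that restricting the primary analysis to people with room to improve is ordinary enrichment. The cut is measured before exposure, applied alike to both groups, and explained in 7.4. That stands, and nothing here requires the cut to go.

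Three stronger readings are tempting, and the documents do not support them.

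- *The exclusion biases the primary result against the app.* The sign and size rest on control means of 60-70. These are Danish figures, and 7.4 says that to the authors' knowledge the instrument has not been used in a general Swedish population. Controls come through social media (6.2.1) and large companies (13), and 94% of pilot participants also came through social media (3.3). If controls score near 55, the difference vanishes. People who sign up at a low point may also regress upward with or without the cut, which would favour the app. On the Hypothesis 1 contrast the cut narrows the null gap, and the larger issue there is baseline imbalance between self-selected users and controls.
- *Section 7.1 contradicts 7.4.* The cut is a listed exclusion in 6.2, and the 7.1 sentence is mainly about missing data, so it can be read as all eligible subjects. But 7.1 does not say so, although it does state a restriction for the intermediate outcomes. This is an inconsistency of wording that needs reconciling.
- *The app could meet the within-group target by artefact alone.* A null rise of at most 4.6 points under these assumptions falls well short of 12. It inflates the change without producing it.

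**Conclusion.** The point holds for change from baseline. In users, the cut alone yields a rise of about 1.5 to 4.6 points by 6 months with no effect, 13-39% of the 12-point aim, given mean 55, SD 19.9, normal scores and a correlation of 0.8 to 0.4. Whether controls correct for this in the 7.3 change contrast depends on their baseline distribution: about -0.5 to -4.9 points against the app at control means of 60-70, and about zero near 55. The documents do not settle which applies. If the control means are 60-70, the cut also removes 31-50% of controls, a loss that 7.4 does not budget for. The correlation and the control mean are assumptions, so the between-group figures are a range and not an estimate of the bias.

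**What to change.** 1. In 7.4, remove the second comparison in "between intervention groups and control group as well as between baseline and 6 months" as an effect target, so that the effect is judged only against controls.
2. Run the same mixed model on all subjects regardless of baseline score, and report it as a sensitivity analysis beside the result for scores of 70 or below. Agreement between the two need not be a condition for the conclusion.
3. State the same primary population in 7.1 as in 6.2 and 7.4.

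The cost is protocol wording and one further model run. Subjects above 70 are excluded from the primary analyses, not from enrolment, so no extra data collection is needed. The downside is that the all-subjects estimate may be diluted if users above 70 cannot improve, which is a reason to keep it as a sensitivity analysis.

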This study is a real-world post-market observational clinical investigation with a control group aimed to evaluate the impact of a digital service in improving well-being by supporting healthy lifestyle habits. A four-armed control condition will allow comparison between a control group recruited among the general population, and three levels of intervention among subscribers. The levels of intervention are I) core functions include self-monitoring, goal setting, action planning, an AI chat and databases with recipes and exercises; II) the same core functions + social support; II) the core functions + social support + individual counselling by a professional health coach. Randomisation of subjects to the different allocation arms is not appropriate because the users or their employers will pay for the digital service and thus choose the level of support.

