## 6. Design of the clinical investigation

### 6.1 Investigational device/Description of exposure

The medical device to be investigated is the mobile phone application (app) LongLife Active®. The app includes three core topics: 1) Healthy diet, 2) Physical activity, and 3) Mental balance. Supplement 4 shows the included intervention components and behavior change techniques. The service includes functions such as tracking and self-monitoring behavior and health outcomes, goal setting, action planning, a database with food recipes, a database with exercises, a database with relaxation exercises, skills training articles and webinars, live events, adjustable push notifications and gamification (rewards). If the user prefers there are options to pay extra for further social support: a version including a community (chat groups and group coaching sessions, live events and physical meetup events), and a version including the community plus the possibility to have a private health coach. The app is assisted by artificial intelligence to direct the support to the individual timely and based on the needs, motivation, preferences, experiences, opportunities, and capabilities of each user. The user decides which functions to use.

The literature review undertaken during the formative phase showed participants wished for interface design and reminders to be customizable, and that the service should be integrated with other services (such as shopping lists). These are examples of aspects that have been regarded to keep engagement over time. With a straightforward design, illustrations, and short video instructions the service is customized for people with low skills in the Swedish language or with low digital and/or health literacy.

No other medical devices or medications are to be used.

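### Section 7.4's minimum of 500 recruits does not assure 25 evaluable subjects in each intervention arm, because users choose their level and no split is stated

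*Protocol*

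**What the plan says.** Protocol section 7.4 gives the size of each group: "a sample size of at least 25 subjects per group is recommended". It then lists two losses. The first is "Expected drop-out rate due to withdrawal and lost to follow-up at six months is 75" per cent. The second rests "on excluding 20% from the analysis due to baseline score" above 70, in line with the pilot figure given just before: "In the pilot study 21% of participants reached 70 points at baseline". From these it concludes that "we need to recruit at least 500 subjects to assure 25 subjects in each intervention arm". Controls are sized separately at 200. The same section then raises the intervention target to 5000, which it justifies by the exploratory secondary outcomes and the mediator and responsiveness analyses.

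Section 3.1 describes "a control group recruited among the general population, and three levels of intervention among subscribers" and rules out randomisation "because the users or their employers will pay for the digital service and thus choose the level of support". Section 6.1 adds: "If the user prefers there are options to pay extra for further social support". Neither section 6.2 nor section 7.4 sets a quota, cap or expected share for Basic, Standard or Premium.

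**The concern.** A total fixes the size of each arm only when the split between arms is controlled or assumed. Here it is neither. The split is decided by purchase, the higher levels cost more, and the protocol makes no forecast of uptake. A promise of 25 in every arm therefore does not follow from 500 recruits.

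The size of each level matters to the plan. Hypothesis 1 in section 5.3 compares the intervention groups with control, hypothesis 2 contrasts Standard and Premium with Basic, and the model in section 7.3 includes intervention level. If one level is sparsely chosen, the comparisons that involve it are weaker than the stated minimum suggests.

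**Working it through.** **Inputs.** From section 7.4: 25 evaluable per group, 75% loss by six months, 20% excluded for baseline score, a stated minimum of 500 and a target of 5000. From section 3.1: three intervention levels. The protocol gives no shares per level, so every share below is an assumption.

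**The stated figure.** The fraction retained is (1 − 0.75) × (1 − 0.20) = 0.20. Recruits per level = 25/0.20 = 125.
- Three levels: 3 × 125 = 375.
- Four groups: 4 × 125 = 500, which matches the printed number exactly.
- With the pilot's 21% in place of 20%: 25/(0.25 × 0.79) = 126.6 per level, so 380 for three levels and 506 for four groups.

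**What 500 delivers.** Evaluable users in total = 500 × 0.20 = 100. Expected number in a level with share s is 100 × s. To expect 25, s must be 25/100 = 25%. If each recruit independently ends up evaluable in that level with probability 0.20 × s, the count is binomial(500, 0.20 × s).

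| Share of least-chosen level | Expected evaluable at 500 | Chance of at least 25 | Recruits for 25 in expectation (125/s) |
|---|---|---|---|
| 33.3% | 33.3 | 95% | 375 |
| 30% | 30 | 85% | 417 |
| 25% | 25 | 53% | 500 |
| 20% | 20 | 15% | 625 |
| 15% | 15 | 1% | 834 |
| 10% | 10 | about 0% | 1250 |

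The chance that all three levels reach 25 together, simulated from the corresponding multinomial, is 85% for an even split, 51% for 40/35/25, 27% for 50/25/25 and 0.5% for 60/25/15.

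**What 5000 delivers.** Evaluable users = 5000 × 0.20 = 1000. A level expects 25 at a share of 25/1000 = 2.5%, with a 53% chance of reaching 25. At 3.5% it expects 35, and the chance is about 97%.

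**Effect on power.** This uses a two-sample t-test with 12 points, SD 19.9 and two-sided 0.05, all from section 7.4. It assumes that the 200 controls suffer the same losses, so 200 × 0.20 = 40 remain. Power for one level against controls is 64% with 25 users, 58% with 20, 39% with 10 and 24% with 5. If controls lose only the 20%, 160 remain, and the figures for 25, 10 and 5 users are 80%, 45% and 26%. The protocol does not give a loss rate for controls.

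**The case against.** The strongest reply is that 500 is not the operating target. Sections 1.6, 6.2 and 7.4 all give 5000, section 15 lists failure to reach 5000 within five years as a reason to terminate, and no analysis or decision is tied to 500. The primary objective in section 5.1 is the service against the control sample. Taken as one pooled contrast, it would use all 100 evaluable users at 500 recruits, however they split. This largely stands, and it limits the practical weight of the point. It does not rescue the sentence. The 5000 is justified on other grounds, not by uneven uptake, and 500 remains the only recruitment minimum given for the primary endpoint.

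Three stronger readings are tempting, and the documents do not support them.
- A reader might infer that a level will certainly fall short. That depends on shares the protocol does not give. With an even split each level expects 33, and 500 exceeds the 375 that three equal levels need.
- A reader might infer that the control group was counted as a fourth arm. The match with 4 × 125 is suggestive, but the derivation is not shown, and the excess over 375 could equally be a margin.
- A reader might blame the modest power at 25 users on the split. That starting value reflects the choice of 25 per group, which is a separate question; only the further fall below 25 users belongs here.

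**Conclusion.** The point holds as a limited one: the minimum of 500 does not have the property that section 7.4 claims for it. It yields 25 evaluable users in the least-chosen level only if that level takes about a quarter of sign-ups, and then with only about a 53% chance. Even an even split gives all three levels 25 with 85% probability, which is short of assurance. These results rest on the protocol's own loss rates, taken as equal across levels and independent between subjects, and on assumed shares.

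While the target of 5000 stands, the consequence is small: a level needs 2.5% of sign-ups to expect 25, or about 3.5% for a 97% chance. The defect is an unstated assumption about the split and an unexplained total. It is not a demonstrated shortfall.

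**What to change.** Replace the sentence in section 7.4 with a requirement per level: n/(0.25 × 0.80) recruits in each level, where n is the evaluable number per group. That is 125 if n stays 25. It rises if n is corrected: the normal-approximation formula with the section's own inputs (12 points, SD 19.9, two-sided 0.05, power 0.90) gives 58 per group, which means 58/0.20 = 290 recruits per level.

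Give the total as that number divided by an assumed smallest share, state the share, and label the result an expected value. Drop *assure*, and explain or replace the 500. State the minimum share needed within the planned 5000: 2.5% to expect 25, or about 3.5% for a 97% chance. Any power quoted by level should use the planned controls after their expected losses.

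The cost is a few lines of text and one restated figure. No extra subjects are needed beyond the planned 5000, and level is known from the subscription, so counting by level is simple. Stating in advance that a level below the minimum will be reported descriptively is optional.
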